**Exclusion criteria**	
1. Pre-injury psychiatric or neurological disease by self-report (e.g., anxiety disorder, ADHD, Parkinson’s disease, etc.) 2. History of diagnosed severe depression (diagnosed pre-injury) 3. History of epilepsy (diagnosed pre-injury) 4. Family history of epilepsy 5. Have had fainting spells or syncope in the last 3 years pre-injury 6. Have significant hearing loss, vision or motor impairment that would prevent them from performing the task 7. Known to be pregnant 8. Consuming medication affecting cortical excitability or recreational drugs^a^ 9. Metal (except titanium) or electronic implants in the brain /skull (e.g., splinters, fragments, clips, cochlear implant, deep brain stimulation, medication pump…) 10. Metal (except titanium) or any electronic device at other sites in your body, such as cardiac pacemaker or traumatic metallic residual fragments 11. Have skin problems such as dermatitis, psoriasis or eczema under the stimulation sites 12. Have had brain stimulation in the past 6 months 13. Have undergone transcranial electric or magnetic stimulation in the past (more than 6 months) which resulted in adverse effects 14. Skull fractures, significant skull defects, skull plates or large vessels occlusions, no significant cortical lesion or atrophy at the site of electrode 15. Having had a seizure at the time of accident or between the injury and starting of the therapy.	

^a^We follow recommendations by McLaren et al. [49], and only exclude drugs that are shown to block tDCS effects (e.g., sodium channel blockers, calcium channel blockers, and NMDA receptor antagonist), while other medications shown to only modulate tDCS effects will be tracked and considered as covariate in the analysis. We will monitor for medication changes as a potential bias on the outcomes of the intervention and report any changes that may occur. If a patient become in need of medications shown to block tDCS effects, they will be excluded from further participation. We will monitor changes in medication and general health through in-person briefing during the first 2 weeks of the intervention, when a researcher is visiting the patient’s house, and via phone calls (e.g. “Have there been any changes in your health or medications since our last phone call?”) during the remaining 3 weeks of the intervention

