#### Participants’ timeline

The flowchart of the procedure is shown in Fig. 2, while a schedule of enrolment, interventions, and assessments is shown in Table 2. The care team as part of the research team identifies potential participants during the cognitive assessment, which is part of the routine care, and invites them to participate. Patients expressing an interest in the study are made aware of possible side effects of brain stimulation and asked to confirm their willingness to participate. During the first in-lab session (T0), following the informed consent procedure, each participant is randomly assigned to one of the two groups (active or sham stimulation) and interviewed by the assessor with a screening questionnaire, including questions about demographic information and health history to evaluate the inclusion/exclusion criteria. We also record information about current medications and information about time since injury, handedness and colour blindness. At this point, participants who don’t meet the eligibility criteria are excluded from further participation.

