##### Outcome assessment (T2)

When the first 10 days of training are complete, the participant will undergo time 2 (T2) assessment. As before, testing involves completing a series of computerised cognitive tasks to measure training gains and transfer (see 3.5.6). This assessment will also include the tests from the WAIS-IV and WMS-IV (Table 3).

**Table 3 Tab3:** Screening tasks

Task	Description
Digit Span (WAIS-IV)	The patient is read a sequence of digits, to repeat forwards, backwards or in ascending order of magnitude (sequence).
Arithmetic (WAIS-IV)	The patient is read a number of mathematical problems increasing from very simple to complex in terms of the amount of information the person has to hold in mind.
Symbol Span (WMS-IV)	Patients are asked to look at a series of symbols for 5 s then choose which symbols they saw from a multiple-choice format, pointing to them in the order they were shown from left to right. The test progresses from only one symbol with the sequence increasing depending on how well people do.
Spatial Addition (WMS-IV)	The patient is shown a grid for 5 s, then a second grid for 5 s. The grids contain blue and red circles. The patient is provided with a number of cards showing red, blue or white circles and asked to place them onto a cardboard grid according to the following rules: Place a blue circle in any place where you saw a blue circle on only one of the pages. Place a white circle in any place where you saw a blue circle in the same place on both pages. Ignore red circles.

##### Training phase 2

Participants will then start the second training phase, involving 3 weeks of working memory training only (no brain stimulation). During this phase, patients will access the training program via internet at home on their own. Manualised weekly phone calls using a semi-structured script will be used to monitor the patients progress and to address any issue they might experience.

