##### Outcome assessment (T3)

When the second 3-week training phase is complete, participants will undergo time 3 (T3) assessment, during which they repeat the same series of computerised cognitive tasks as in T2 (Table 4).

**Table 4 Tab4:** List of outcome measures

TASK	DESCRIPTION	Target functions
Simple Reaction Time	Respond to each stimulus, with varying response-stimulus intervals.	Vigilance
Go/No-Go	It employs a continuous stream of two different stimuli for which a binary decision must be made, such that one stimulus type requires a response (go) and the other stimulus type requires the participant to withhold a response (no-go).	Executive control
2-Choice Reaction Time	Indicate the colour of each stimulus (2-choice responses; 50% each choice).	Vigilance
Dual task	Complete the 2-choice reaction time task while silently counting the number of each colour of stimuli presented. Count probe for one colour at the end of each set.	Executive control
Flanker	A central target stimulus is presented with flanking stimuli (flankers) on two sides that are either the same as (congruent) or different than (incongruent) the central target stimulus. The participant must decide and respond regarding a feature of the central stimulus (e.g., red or black) while ignoring/filtering the flanking stimuli.	Executive control
Item Working memory	Indicate whether a probe item was present or absent in a preceding study set of 2–6 items (50% present).	Working memory
Location working memory	Indicate whether a probe item was present or absent in the same position in a preceding study set of 2–6 locations (50% present).	Working memory
Visual search	Locate and indicate orientation (upright vs. inverted; 50% each) of a target among different shape distractors that are a different colour (feature search) or the same colour (conjunction search) as the target.	Orienting and Selection
Fixed visuo-spatial n-back task	Participants must attend to a visual stream of information that is presented sequentially and look for matches, pressing a button upon seeing a “match”. Three levels of difficulty will be used (n = 1,2,3)	Working memory

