##### Outcome assessment (T4)

A final follow-up assessment, identical to the one at T2 and T3, will be carried out 1 month after the completion of the intervention, to assess maintenance of working memory improvements and transfer.

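### The medication rule in footnote a to Table 1 ends participation after randomisation with no time limit, so T3 and T4 (and T2 if early) go uncollected for a reason that may be related to outcome

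*Protocol article*

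**What the plan says.** Under Eligibility criteria, footnote a to Table 1 limits the medication exclusion to agents that block the stimulation effect: the investigators "only exclude drugs that are shown to block tDCS effects (e.g., sodium channel blockers, calcium channel blockers, and NMDA receptor antagonist". Drugs that only modulate the effect are tracked and used as a covariate, and those patients stay in. For a blocking drug that becomes necessary later, the footnote says: "If a patient become in need of medications shown to block tDCS effects, they will be excluded from further participation".

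The footnote then describes how medication and general health are followed: "through in-person briefing during the first 2 weeks of the intervention", and by phone "during the remaining 3 weeks of the intervention". Training phase 2 describes those later weeks as "involving 3 weeks of working memory training only (no brain stimulation".

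Participants' timeline places assignment at the first session (T0), where "each participant is randomly assigned to one of the two groups (active or sham stimulation". The later assessments are T3 ("When the second 3-week training phase is complete, participants will undergo time 3 (T3) assessment") and T4, which "will be carried out 1 month after the completion of the intervention". No section provides for continued assessment of a patient to whom the medication rule has been applied.

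**The concern.** The rule acts on patients who have already been randomised, and it is triggered by something that happens afterwards. A newly needed drug can reflect a change in health, and a change in health can be related to cognitive performance. The assessments that are then missed may therefore be missing for a reason linked to the outcome, and the comparison of the groups as randomised is no longer complete.

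The rule's link to its purpose is also weakest in weeks 3-5. By then every stimulation session has been given, yet the text does not stop the rule there. A patient who starts a blocking drug in week 4 would have received the full stimulation course and T2, and would then contribute nothing at T3 or T4. The Outcome measures section rests the maintenance question on T3 and T4, and counts training gain over the whole course of training as primary. An analysis plan written later cannot recover assessments that were never made. The trial is also small: 40 patients, below the 48 its own calculation gives, with no stated allowance for loss.

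**Working it through.** **Reach of the rule**

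1. Assignment is at T0, before any stimulation, so every application of the rule comes after randomisation.
2. The exclusion sentence names no period. The monitoring that would bring a new drug to light covers weeks 1-2 in person and weeks 3-5 by phone.
3. Stimulation ends after session 10, at the end of week 2. T2 follows, then three weeks of training alone, then T3, then T4 one month later.
4. So a drug needed in weeks 1-2 costs T2, T3 and T4. One needed in weeks 3-5 costs T3, T4 and the remaining training sessions. Data recorded before the stop remain.

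**Reproducing the plan's sample size**

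Inputs from Sample size calculation: effect size 0.73, alpha .05 (sidedness not stated), power 0.80, stated N about 48. Formula: n per arm = 2(z_alpha + z_beta)² / 0.73², with 0.73² = 0.5329.

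- One-sided: 2(1.645 + 0.842)² / 0.5329 = 23.2, so 24 per arm and N = 48. The t-test gives 23.9 per arm, again N = 48.
- Two-sided: 2(1.960 + 0.842)² / 0.5329 = 29.5, so 30 per arm and N = 60. The t-test gives 30.4 per arm, N = 62.

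The stated 48 is reproduced only as a one-sided test, so both bases are shown below.

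**Power after loss**

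The planned number is 20 per arm (Randomization and blinding). The document gives no rate for starting a blocking drug, so a loss of 0 to 4 per arm is assumed. Two-sample t-test, effect size 0.73, alpha .05:

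| Lost per arm | Left per arm | Power, one-sided | Power, two-sided |
|---|---|---|---|
| 0 | 20 | 73.3% | 61.4% |
| 1 | 19 | 71.3% | 59.1% |
| 2 | 18 | 69.2% | 56.7% |
| 3 | 17 | 66.9% | 54.2% |
| 4 | 16 | 64.5% | 51.5% |

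From 0 to 4 lost per arm the fall is 73.3 − 64.5 = 8.8 points one-sided and 61.4 − 51.5 = 9.9 points two-sided, or roughly 2 to 2.5 points for each patient lost per arm.

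**Bias**

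Let m be the mean of the patients who remain in one arm, in SD units.

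- Unfavourable case (assumed): 2 of 20 are lost in the active arm only, and each would have scored 1 SD below the rest. The mean for all 20 would be (18m + 2(m − 1)) / 20 = m − 0.10. The mean observed from 18 is m, so it is too high by 0.10 SD, and 0.10 / 0.73 = 14% of the planning effect.
- Neutral case (assumed): the same number of similar patients is lost in both arms. Both means shift by 0.10 SD and the net bias is 0.10 − 0.10 = 0.

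**The case against.** Several points on the other side are sound.

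- **Deletion.** A reader might infer that the rule discards the patient's outcomes. The text stops further participation only. It does not say that collected data are deleted or that the patient leaves the analysis. This stands: the loss is of later assessments.
- **Loss of the whole patient.** A reader might infer that repeated measures ANOVA would also drop the patient's T1 and T2. The data analysis section names mixed and repeated measures ANOVAs as examples of appropriate methods and does not fix the handling of missing data. A T1-T2 contrast does not need T3. This stands.
- **Weeks 3-5.** The exclusion sentence does not name them, and the phone calls also serve to track modulating drugs and to report changes. That the rule was meant to apply then is an inference. But nothing in the text excludes those weeks, so the rule can be applied there as written.
- **Rationale.** A reader might infer that the rule has none after stimulation ends. The footnote does give a reason, namely that medication changes may bias the outcomes of the intervention. That reason supports recording the drug. It does not require that measurement stop, and the same footnote keeps patients on modulating drugs in the study.
- **Difference between arms.** Patient and assessor are blinded until the end of the intervention, so the rule is applied without knowledge of the arm. This makes differential loss less likely. It does not exclude it, because health changes after treatment may themselves differ by arm.
- **Reporting.** The promise to report medication changes gives transparency but does not supply the missing outcomes.

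**Conclusion.** The point holds in a limited form and should be corrected. The protocol fixes a rule, open-ended in time, that stops the assessment of randomised patients because of an event after randomisation that may be related to outcome. It can take effect when no stimulation remains to be given.

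The size is uncertain because no rate is stated, and few patients may be affected. On the assumed losses, power falls by about 4 points with 2 lost per arm (73.3% to 69.2% one-sided; 61.4% to 56.7% two-sided) and by 9 to 10 points with 4 lost per arm. The low starting power is a separate sample-size matter. Net bias ranges from zero to about 0.10 SD over the two scenarios worked. The upper figure describes one unfavourable case and is not an expected value.

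The documents do not support the stronger claims that existing data are deleted, that whole patients necessarily drop out of the analysis, or that the loss will differ by arm.

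**What to change.** Separate the exclusion rule from outcome assessment in footnote a:

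- State that the remaining scheduled T2-T4 assessments are completed where the patient consents, and that the patient is analysed in the allocated group.
- State the period in which the rule applies, so that footnote a and Training phase 2 can be read together.
- Record the drug and its start date.
- Add a sensitivity analysis without patients who started a blocking drug before the last stimulation session. It selects on a post-randomisation event, so it supports the as-randomised analysis and does not replace it.

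Whether stimulation or training continues is for the clinicians, and no view is taken here. If training stops, the n-level training gain after that point may not be recovered, so the change restores the assessment visits but perhaps not the whole of that measure.

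The cost is protocol wording plus visits that are already scheduled. The statistical downside is slight dilution of the effect if a drug started in weeks 1-2 blocks later sessions. The sensitivity analysis would show how much this matters.

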### Recruitment

Forty adults between the age of 18 and 69 years will be recruited through the Community Brain Injury Service. Patients will be randomly assigned to one of two experimental groups: an active (or right-sided tDCS) group and a control (or SHAM) group. All patients will receive WM training. As there is evidence that age modulates individual responses to both tDCS [50–52] and training regimens [53, 54], the two groups will be age-matched in two age subgroups: those aged between 18 and 45 years and those aged between 46 and 69 years, randomised within age range. Other factors may also influence the impact of the intervention on patients, including medications, time since injury, baseline performance, and these factors will be included as regressors in the analysis whenever appropriate. To reduce the variability due to different locations of lesions, patients with lesions underneath the electrodes (that could modify the induced electric field) will be excluded. Finally, as explained in the following, patients will only be included if they present with a working memory deficit, but no general intellectual impairment.

As the aim of this research is to improve working memory, only participants with a working memory impairment will be included. As we are focusing on improving a documented working memory deficit, we will not attempt to distinguish between pathologies (unless otherwise determined by the exclusion criteria for tDCS, e.g. a lesion underneath the electrodes), rather we will screen patients based on working memory performance. Final analysis will explore differences between pathologies. To identify a working memory impairment, cognitive tests from the Wechsler Adult Intelligence Test (WAIS-IV) and the Wechsler Memory Scale (WMS-IV) will be administered. These tests are administered to every patient as part of the routine care protocol. We will use the following scores:
A WAIS-IV Full-Scale Intelligence Quotient (FSIQ) lower than 70: this score will identify any patients with significant intellectual impairment. The FSIQ will also be used as a covariate in the analysis to control for the effects of reduced overall intellectual ability rather than a specific working memory issue.A WAIS-IV Working Memory Index (WMI) score, obtained as a combination of the digit span score and the arithmetic score in the WAIS-IV, smaller than 85: this score identifies an auditory working memory impairment.A WMS-IV Visual Working Memory Index (VWMI) score, below 85 identifies weakness in visuospatial working memory.

The WAIS-IV and WMS-IV above are co-normed on a large sample (mea*n* = 100; SD = 15). To be included in the study, a patient will have a FSIQ > 70 and either a WMI or a VWMI or both < 85, which means we adopt a criterion score of one standard deviation below the mean. We use working memory indices that are a combination of auditory and visual working memory to identify an objectively defined working memory deficit. We will also run an exploratory post-hoc analysis factored by type of baseline WM deficit to ascertain if there are any modality specific benefits*.* Although this score reflects at least mild impairment, a weakness in working memory would be large enough to potentially improve with training.

### Sample size calculation

The chosen sample size is based partly on the available literature that examines the effects of cognitive training on healthy young and older volunteers and additional pilot data collected in our laboratory from healthy young and elderly adults. Specifically, a statistical power analysis was performed for sample size estimation, based on data from Au et al. [39], comparing the ACTIVE (right-tDCS, 20 subjects) to the CONTROL (SHAM, 22 subjects) group. The effect size (ES) in this study was 0.73, considered to be medium to large using Cohen’s criteria [55]. With an alpha = .05 and power = 0.80, the projected sample size needed with this effect size (GPower 3.1) is approximately *N* = 48 for this simplest between group comparison.

Evidence has shown that individuals with low initial performance respond better to brain stimulation [56]. As we expect ABI patients in our sample to have low baseline performance, due to our selection criteria, we may also expect them to respond better to the intervention, therefore showing larger effects. Assuming, as explained above, that larger effects could reasonably be expected in a clinical population, our proposed sample size of 40 will be adequate for the main objective of this study. A post hoc power analysis will be conducted to assess if the sample size is appropriate to detect differences in a clinical population such as ABI.

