### Data collection, management, analysis, and monitoring

Accuracies and reaction times at trial level will be collected, alongside the ‘n’ level for each block. Data will continuously be monitored for completeness and consistency. Data entry will be double-checked, and data quality will be ensured based examination of ranges. Prior to statistical analysis, we will test the distribution of the scores. We will analyse the data using appropriate statistical methods, including mixed and repeated measures ANOVAs, with factors of group and test variables. Variables potentially modulating the outcome of the intervention (such as age or time since injury) will considered as regressors in the analysis. Scores that are non-normally distributed will be analysed with non-parametric tests. Significant main effects and interactions (*p* < .05) will be followed by post-hoc tests corrected for multiple comparisons. Dependent variables on the computerized tasks will include mean reaction time (RT) and accuracy (% correct). The research team will analyse the data with a combination of SPSS, JASP, R, Python, and MATLAB.

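### The planning figure of 48 matches only a one-sided test while the planned ANOVAs need 62, and N = 40 rests on a larger effect that is never quantified

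*Protocol article*

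**What the plan says.** The Sample size calculation section of the protocol article takes its effect size from a cited comparison of active (20 subjects) with sham stimulation (22 subjects): "The effect size (ES) in this study was 0.73, considered to be medium to large using Cohen’s criteria". It continues: "With an alpha = .05 and power = 0.80, the projected sample size needed with this effect size (GPower 3.1) is approximately" 48, "for this simplest between group comparison". It does not say whether alpha is one- or two-sided.

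The next paragraph argues that people with low initial performance respond better to stimulation, and that the selection criteria should yield low baselines and so larger effects. On that assumption, "our proposed sample size of 40 will be adequate for the main objective of this study". It gives neither the size of the larger effect nor the power at 40. It closes with a check after the event: "A post hoc power analysis will be conducted to assess if the sample size is appropriate to detect differences in a clinical population".

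Two other sections bear on this. Data collection, management, analysis, and monitoring plans methods "including mixed and repeated measures ANOVAs, with factors of group and test variables", with significance at p < .05. Recruitment sets the entry rule as a full-scale IQ above 70 and "either a WMI or a VWMI or both < 85".

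**The concern.** Three steps in the sample-size argument do not hold together.

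- **The planning figure does not match the planned test.** An ANOVA F-test for two groups is equivalent to a two-sided t-test, and the article declares no one-sided test. A requirement of 48 at 0.73 looks too small for it.
- **The step from 48 to 40 has no number behind it.** A larger effect is assumed, but the reader cannot tell how much larger it must be. The reason given is also only partly secured by the entry rule. A patient with an auditory deficit alone (WMI below 85, VWMI normal) qualifies, while the trained task is visuo-spatial (Working memory training section). Selection therefore does not guarantee low baseline performance on that task.
- **The planned check may be empty.** Power computed after the trial at the observed effect carries no information beyond the p-value.

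At stake is how a non-significant result is read. If the true effect were 0.73, the unadjusted two-sided comparison would miss it about 39% of the time (100% − 61%). The article gives readers no figure from which to see this.

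**Working it through.** **Inputs.** From Sample size calculation: d = 0.73 (read as a standardised mean difference), alpha .05, target power 0.80, stated requirement about 48, chosen N = 40, source arms 20 and 22. From Randomization and blinding: 20 patients per arm.

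**Formula.** Two-sample t-test with n per arm: df = 2n − 2 and noncentrality δ = d·√(n/2). One-sided power is P(T > t at 0.95); two-sided power is P(|T| > t at 0.975), with T noncentral t(df, δ).

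**1. Reproducing 48.** For n = 24, δ = 0.73·√12 = 2.529 and df = 46.
- One-sided: critical value 1.679, power 0.801. With n = 23, power is 0.786. The requirement is 48, as stated.
- Two-sided: critical value 2.013, power 0.697. The stated figure is not reproduced.

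Other variants were tried. Allocation in the ratio 20:22 gives 48 one-sided and 63 two-sided. A Wilcoxon test gives 52 to 56 one-sided and 64 to 72 two-sided (relative efficiency 0.955 to 0.864). A two-group F-test with f = 0.73/2 = 0.365 gives 62. Every variant that yields 48 is one-sided.

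**2. Two-sided requirement.** n = 30 gives 0.794 and n = 31 gives 0.807, so 62 patients are needed.

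**3. Power at N = 40.** For n = 20, δ = 0.73·√10 = 2.308 and df = 38.
- Two-sided: critical value 2.024, power 0.614.
- One-sided: critical value 1.686, power 0.733.

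**4. Effect needed for 80% power at 20 per arm.** Solving for d gives 0.909 two-sided (0.909/0.73 = 1.25, or 25% above 0.73) and 0.801 one-sided (about 10% above).

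**5. Dropout (assumption; the article gives no rate).**

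| Loss | Per arm | Two-sided power at 0.73 | d for 80% power |
|---|---|---|---|
| 0% | 20 | 61% | 0.91 |
| 5% | 19 | 59% | 0.93 |
| 10% | 18 | 57% | 0.96 |
| 15% | 17 | 54% | 0.99 |
| 20% | 16 | 52% | 1.02 |

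**6. Baseline adjustment (assumption; no correlation is given).** If 0.73 is an unadjusted effect and baseline and outcome correlate at r, the effective d is 0.73/√(1 − r²). For r = 0.3, 0.5 and 0.6 this is 0.77, 0.84 and 0.91, with two-sided power at N = 40 of about 65%, 74% and 80%.

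**7. Precision of 0.73.** With 20 and 22 subjects, t = 0.73·√(20·22/42) = 2.363 on 40 df. Inverting the noncentral t gives a 95% CI for d of about 0.10 to 1.35. This interval contains 0.91, but also much smaller values: at d = 0.50, N = 40 has 34% power two-sided.

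**8. Post hoc power at the observed effect, N = 40.** Setting δ to the observed t on 38 df, p = .05 (t = 2.024) gives 51%, p = .20 (t = 1.304) gives 25% and p = .50 (t = 0.681) gives 10%. Each p-value maps to one power value, so the step adds nothing.

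**The case against.** A reader might infer that the article claims 80% power for 40 patients, or that 0.73 is the effect assumed for 40. It does neither. It ties 0.73 and 80% to 48, shows openly that 40 is fewer, and makes adequacy conditional on a larger effect. This objection stands.

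A reader might also conclude that the claim of adequacy is false. The documents do not support that either. The effect needed is 0.80 one-sided or 0.91 two-sided, both within the source study's interval, and the evidence cited for better response at low baseline cannot be examined here. The supportable criticism is that the claim is unsupported as written.

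Sidedness is inferred from arithmetic. The primary objective (Aims and objectives) is worded directionally, as superiority, and the analysis section lists ANOVAs among appropriate methods, with non-parametric tests for non-normal scores. The primary test is therefore not rigidly fixed. But a directional objective does not make an F-test one-sided, no one-sided test is declared, and even on a one-sided basis 40 gives only 73% at 0.73.

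The article also plans regressors, including baseline performance where appropriate, which could recover power; 61% is the unadjusted figure and must be labelled so. The sample-size section does not rely on this gain.

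Finally, the article does not say which effect the post hoc power analysis will use. The criticism applies only if it is the observed one.

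**Conclusion.** The point holds in a limited form. On the article's own inputs, 48 corresponds to a one-sided test, whereas the non-directional tests it plans need 62; 48 gives 70% two-sided. N = 40 is below 80% power at 0.73 on either basis: 61% two-sided and 73% one-sided. Its justification depends on an effect about 25% larger than 0.73 (two-sided) or 10% larger (one-sided), which the article never states and which the entry rule does not secure.

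These figures assume that 0.73 is a standardised mean difference, that the comparison is a two-group t-test or its F equivalent, that all 40 patients are evaluable, and that there is no covariate adjustment. Dropout would lower power; adjustment for a correlated baseline would raise it. The finding is not that 40 patients cannot suffice, but that the stated reasoning does not show that they do.

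**What to change.** Keep N = 40 and rewrite the sample-size section to:

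1. State two-sided alpha .05, in line with the planned ANOVA tests.
2. Correct the requirement at d = 0.73 from 48 to 62 (31 per arm).
3. State that 40 patients give 61% unadjusted two-sided power at d = 0.73, and 80% only for d of at least 0.91. Add that, under an assumed 5% to 20% dropout, this threshold becomes about 0.93 to 1.02.
4. Note that baseline adjustment may raise power by an amount that depends on the baseline-outcome correlation.
5. Replace the claim of adequacy with this explicit detectable effect.
6. Replace the post hoc power analysis with the baseline-adjusted group difference and its 95% CI, and report whether the interval, on the same standardised scale, excludes 0.73.

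The cost is wording and a less favourable stated power. No extra patients are needed. The rewrite does not remove the shortfall at 0.73; it makes it visible and gives a non-significant result an interpretable interval.
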